## Abstract

**Background:**

Negative workplace behaviour among nurses is an internationally recognised problem, despite the plethora of literature spanning several decades. The various forms of mistreatments and uncaring attitudes experienced by nurses include workplace aggression, incivility, bullying, harassment and horizontal violence. Negative behaviour has detrimental effects on the individual nurse, the organisation, the nursing profession and patients. Multi-level organisational interventions are warranted to influence the “civility norms” of the nursing profession.

**Objective:**

The aim of this study is to investigate the self-reported exposure to and experiences of negative workplace behaviours of nursing staff and their ways of coping in regional acute care hospitals in one Local Health District (LHD) in NSW before and after Respectful Workplace Workshops have been implemented within the organisation.

**Methods:**

This study employs a mixed methods sequential explanatory design with an embedded experimental component, underpinned by Social World’s Theory. This study will be carried out in four acute care regional hospitals from a Local Health District (LHD) in New South Wales (NSW), Australia. The nurse unit managers, registered nurses and new graduate nurses from the medical and surgical wards of all four hospitals will be invited to complete a pre-survey examining their experiences, perceptions and responses to negative workplace behaviour, and their ways of coping when exposed. Face-to-face educational workshops will then be implemented by the organisation at two of the four hospitals. The workshops are designed to increase awareness of negative workplace behaviour, the pathways to seek assistance and aims to create respectful workplaces. Commencing 3 months after completion of the workshop implementation, follow up surveys and interviews will then be undertaken at all four hospitals.

**Results:**

The findings from this research will enhance understanding of negative workplace behaviour occurring within the nursing social world and assess the effectiveness of the LHD’s Respectful Workplace Workshops upon the levels of negative workplace behaviour occurring. By integrating qualitative and quantitative findings it will allow for a dual perspective of the social world of nurses where negative and/or respectful workplace behaviours occur, and provide data grounded in individuals lived experiences, positioned in a macro context

**Conclusions:**

It is expected that evidence from this study will inform nursing practice, and future policy development aimed at creating respectful workplaces.

**Trial Registration:**

Australian New Zealand Clinical Trials Registry (Registration No. ACTRN12618002007213; 14 December 2018).

**International Registered Report Identifier (IRRID):**

PRR1-10.2196/18643

## Introduction

### Background

Various forms of negative workplace behavior have been reported across the health care professions, including in nursing [1,2], allied health professions [3], and medicine [4]. In addition to making working life unpleasant and stressful, the existence of a negative workplace culture risks patient safety [4]. The term negative workplace behavior is a euphemism that encompasses a wide range of undesirable behaviors, such as bullying (either physical or otherwise), harassment, horizontal violence, and incivility. The commonality is that the behaviors occur in the workplace; however, there are differences in definitions [2], as does the identity of the perpetrators. Bullying is characterized by repetitive acts that are directed at a person or group by one or more perpetrators in a position of power [5], whereas horizontal violence occurs between peers in equal positions [6]. In addition to these reported high-intensity behaviors, it has been suggested that incivility, as defined by Pearson et al [7] as “low-intensity deviant behavior with ambiguous intent to harm the target, in violation of workplace norms,” occurs daily and is accepted as a normal part of the nursing *socialization process*. Owing to the varying terms used in the literature, the term *negative workplace behavior* will be used throughout this paper to be inclusive of bullying, harassment, horizontal violence, and incivility.

Negative workplace behavior in nursing has been extensively explored, and there is a great variation in the reported incidences [1,2]. Regardless of this variation, it is widely accepted that negative workplace behavior continues to be a significant issue impacting nurses both personally and professionally [8,9] not only in Australia but internationally [2]. However, caution is necessary while comparing the reported prevalence rates of negative workplace behavior between countries due to differences in terminology, the lack of definitional consensus, and the multiplicity of assessment measures used in different studies. Reporting is also influenced by pre-existing intercultural differences in the tolerance and perceptions of bullying or similar behaviors [2,10].

Although negative workplace behavior entails the actions of an individual or a group, organizational culture, workloads, and leadership styles have all been shown to affect its occurrence [10]. It has been suggested that organizations seeking to mitigate negative workplace behaviors should aim to improve organizational processes that inform the management of bullying, implement skills-based training in communication and conflict management, and aim to promote accountability, transparency, and respectful peer alliances [11,12]. In the literature, there is little evidence of effective strategies that have been implemented in acute care settings to address negative workplace behavior experienced by nurses [2,13]. Of 18 previous quantitative studies that were recently reviewed critically, as reported elsewhere [2], all were descriptive and exploratory, as opposed to interventional studies. The available literature sanctions intervention at multiple levels to influence the *civility norms* of the nursing profession, clearly emphasizing on the modification of culture and practice [13]. It is evident in nursing as well as other disciplines that interventions with integrated, organization-wide approaches improve *civility* [13-16], whereas interventions focused on individuals have less impact [17,18]. Therefore, rather than focusing on individual interventions, such as targeting new graduate nurses (NGNs) to improve resilience [19], the research methodology described in this paper takes a multi-level approach. The protocol targets NGNs, registered nurses (RNs), and senior RNs in managerial positions. The study will investigate participants’ experiences of negative workplace behavior and their ways of coping when exposed in an environment where an intervention was being implemented at an organizational level concurrently, at the time the research was being undertaken.

### Theoretical Framework

The theoretical framework that underpins this research protocol is the Social Worlds Theory [20]. Social Worlds Theorists explain society as shaped and upheld via repeated interactions between individuals [21] and that society as a whole can be conceptualized as consisting of a mosaic of social worlds that both touch and intersect [22]. These social worlds refer to groups where there is *a set of common or joint activities or concerns, bound together by a network of communication* [23]. Social worlds develop around one primary activity (eg, delivery of patient care). There are also sites where these activities occur (eg, within the hospital setting) and technology relating to performing the activities is always involved (eg, clinical and technical skills). Each individual within the social world is engaged in a relevant activity; however, some individuals are, or believe themselves to be, more *authentically* belonging and more suited to that world [24]. Claims of authenticity can lead to conflict and power struggles and consequently to the creation of excommunicated individuals of social subworlds [24]. The ongoing conflict and the creation of subworlds within the primary social world of nursing is evident, and tension and conflict manifest in the form of negative workplace behavior.

## Methods

This study is ongoing and has been registered with the Australian New Zealand Clinical Trials Registry (Registration No. ACTRN12618002007213; December 14, 2018).

### Study Aims

The aim of this study is to investigate the self-reported exposure to and experiences of negative workplace behaviors of nursing staff and their ways of coping in regional acute care hospitals in one local health district (LHD) in New South Wales before and after Respectful Workplace Workshops have been implemented within the organization.

### The Study Design

This study uses a mixed methods, sequential explanatory design [25] with an embedded experimental component [25,26]. Data collection will occur in 3 distinct strands:

Strand 1: an initial survey before the delivery of the Respectful Workplace Workshops by the organization (quantitative).Strand 2: follow-up surveys after conducting the workshops at 2 of the 4 hospitals involved in the study (quantitative).Strand 3: interviews with nursing staff from across all the hospitals involved in the study (qualitative).

The sequence of the strands is presented in Figure 1. The mixed methods approach recognizes that neither quantitative nor qualitative study designs alone are able to capture the nuances of particular phenomena, whereas the combination of both takes advantage of their respective strengths [25]. Integrating qualitative and quantitative findings will allow triangulation and a broader perspective of the participants’ social worlds, with data grounded in individuals’ lived experiences, positioned in a macro-organizational context [27].

**Figure 1 figure1:**
[figure not shown]
Flowchart showing the entire research process for the mixed methods study.

### Stakeholder Engagement

The research team collaborated early in the study design process with stakeholders from within the organization. Consultation took place with the LHD Respectful Workplace Workshop delivery team, the research committee, the executive director of nursing, and the directors of nursing, nurse unit managers (NUMS), and clinical nurse educators (CNEs) at each proposed hospital site. Stakeholder engagement in health care research is advocated to increase collaboration between researchers and users, thereby increasing research impact and knowledge translation [28]. This collaborative design process allowed for the negotiation of included hospitals to meet both researcher and organizational needs by assisting and aligning with the organization’s plan to deliver Respectful Workplace Workshops at the proposed sites. The consultation also allowed the identification of potential barriers in undertaking the study, including teaching workloads for the workshop delivery team and clinical workload and time required away from the wards for staff to attend the workshops.

### The Respectful Workplace Workshops

The Respectful Workplace Workshops will occur in the intervening period of data collection between strand 1 and strand 2. The workshops comprise 3 copyrighted face-to-face training modules developed for LHD delivery. The aim of the modules is to promote respectful workplace behavior by improving communication between staff members with the aim to recognize, manage, and mitigate negative workplace behavior [29]. These workshops have previously been delivered at other metropolitan hospitals within the LHD but not at those selected for this study.

The Respectful Workplace Team, an education division within the LHD, delivers the workshops, with all workshop facilitators having completed relevant prior training. The workshops require staff to attend face-to-face teaching sessions. Modules 1 and 2 require 2 hours of contact time and, to assist with rostering, the team has combined modules 1 and 2 into a single 4-hour workshop. Module 3 is only for nurse unit managers and requires attendance for a further 4 hours of face-to-face contact. The workshops will be made available to staff on various days over a 3-month period to increase attendance and minimize disruption.

The modules use a combination of training methods, including role-play, brainstorming, didactic teaching with PowerPoint presentations, and workbooks. The first two modules aim to challenge participants and encourage reflection on responsibilities and contributions to support a respectful workplace. These modules provide participants with a structured conversation template to assist with clear, direct, and respectful communication, allowing for role-playing of these conversations to assist the translation of theory into practice. The third module explores the manager’s role in supporting a respectful workplace and aims to improve managerial skills by using resolution pathways and coaching of other staff. Although workshop attendance is not compulsory, the directors or nursing have agreed to support and encourage attendance and roster staff accordingly.

### Setting, Sampling, and Participants

Study setting, sampling, and participant recruitment will be based on the inclusion criteria pertinent to the research aims [30]. To minimize selection and participant bias, comprehensive and rigorous criteria have been developed. Potential hospitals and units for inclusion were selected in consultation with the Respectful Workplace Team, the members of which are employed in the LHD to deliver Respectful Workplace Workshops in the hospitals. The selection of hospitals and units was based on the presence of minimal or no previous attendance by nurses at the Respectful Workplace Workshops. A total of 9 employees across the 4 hospitals were identified as having potentially attended the workshops previously at other hospitals within the health district. The hospitals chosen are of similar size, with similar service availability and case mix. Regional hospitals were selected because the phenomenon under investigation is of significant concern in nonmetropolitan locations, where ongoing staffing and recruitment issues exist [31]. Being in the same LHD, all 4 hospitals have the same centralized executive leadership, are subject to the same bullying and negative workplace behavior policies, and are subject to the same human research ethics committee governance processes. In total, 2 of the 4 hospitals were assigned to have the Respectful Workplace Workshops delivered within the 6-month study period; these hospitals (A and B) are referred to as the *intervention sites* in Figure 1. The other 2 hospitals did not have the workshop delivered until after data collection of strands 2 and 3 was completed. Those hospitals (C and D) are referred to as the *control sites* in Figure 1.

This study included 12 wards or units across 4 nonmetropolitan, regional acute care hospitals within the same New South Wales LHD. The units were selected on the basis that they were general medical or surgical wards, where most NGNs were employed.

Targeted study participants may be categorized as follows:

NGNs in their first 12 months of practice following the completion of a Bachelor of Nursing degree.RNs who had been employed for more than 1 year at a minimum of 0.6 full-time equivalent.Senior RNs are employed in permanent leadership roles, who have managerial responsibilities for other staff members and patients, including NUMs, CNEs, and clinical nurse specialists.

Nursing staff known to have attended the workshops previously will be excluded from selection and others who indicate in the initial survey screening questions that they had previously attended the workshop will also be excluded from the data analysis. Owing to the relatively low number of previously exposed participants spread across 12 wards or units, the risk of contamination bias at a site level was considered minimal.

The participants will be allocated into clusters according to hospitals at which they are working; thus, they will be employed at hospitals where the workshops were either delivered or not delivered. Nested sampling will be undertaken for the qualitative and quantitative components of the study. The sample of the qualitative component is a subset of those who participated in the quantitative components. Survey participants will be a volunteer sample of nursing staff working in the medical and surgical wards in all 4 participating hospitals. The sample for the qualitative component of the study will be purposively chosen from survey respondents who will volunteer to be interviewed to represent the roles of the nurses and sites where they are working.

The total target population is 230 at the time of writing this paper, which includes 64 NGNs, 154 other RNs, and 12 senior RNs with managerial roles. Assuming a 30% response rate (n=69), 5% type 1 error, and 80% power to detect an effect size equivalent to 0.7 of the SD, it is anticipated that it will be necessary to recruit 35 participants from the hospitals where the Respectful Workplace Workshops will be delivered and 35 from those where no workshops are conducted.

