### Conclusions

The findings from this research will add to the volume of literature on negative workplace behavior in the health care professions; however, it will add new perspectives through using multiple, previously validated survey instruments in combination with qualitative, in-depth interviews. The integration of quantitative and qualitative methods will allow for a dual perspective contextualized with the theoretical lens of the Social Worlds Theory to provide data grounded in individuals’ lived experiences and positioned in a macro-organizational reality. A further perspective is provided by the opportunity to perform the research in conjunction with the delivery of the LHD’s Respectful Workplace Workshops. By collecting pre- and postworkshop data and from sites both exposed and not exposed to the workshops, it is expected to add insights into the efficacy of such interventions. It is anticipated that evidence from this study will inform future nursing practice and policy development aimed at creating respectful workplaces.

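### The experimental label and effectiveness claim rest on two hospitals per group, no described randomisation and a comparison at strand 2 only

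*Protocol article*

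**What the plan says.** **Label and claim.** The Study Design section describes a mixed methods study "with an embedded experimental component", and the Methods part of the Abstract uses the same label. The Results part of the Abstract says the study will "assess the effectiveness of the LHD’s Respectful Workplace Workshops upon the levels of negative workplace behaviour occurring". The closing Conclusions, referring to pre/post data from exposed and unexposed sites, say "it is expected to add insights into the efficacy of such interventions", and expect the evidence to inform practice and policy.

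**Allocation.** In Setting, Sampling, and Participants, "2 of the 4 hospitals were assigned to have the Respectful Workplace Workshops delivered within the 6-month study period" (hospitals A and B); C and D serve as controls and receive the workshops later. No section mentions a random element. Stakeholder Engagement says that collaboration allowed the "negotiation of included hospitals to meet both researcher and organizational needs by assisting and aligning with the organization’s plan to deliver Respectful Workplace Workshops". The unit is the hospital: "The participants will be allocated into clusters according to hospitals at which they are working".

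**Comparison.** Quantitative Data Analysis names t tests for continuous variables and states that intervention and control sites will be compared on the NAQ-R and WCQ at strand 2. It gives the strand 1 survey no role in that comparison, although Principal Findings describes a before-and-after approach.

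**The concern.** A study that calls itself experimental and promises to assess effectiveness leads its reader to expect that a difference between the groups can be attributed to the workshops. Here it cannot, for two reasons.

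- **Standing differences.** A comparison at strand 2 alone contains whatever differences in workplace culture the hospitals had before any workshop. The baseline survey could remove these, but the stated comparison does not use it.
- **Local change.** With two hospitals per group, an event in one hospital affects half of that group. Potential Limitations concedes that staff changes or a change of manager may occur during the study. Baseline adjustment would not remove such an event.

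The findings are meant to feed into policy, so a claim stronger than the design can bear matters outside the study.

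**Working it through.** **1. The plan's own figure.** Inputs from Setting, Sampling, and Participants: difference 0.7 SD, type I error 5% (two-sided assumed), power 80%, 35 per group. For independent nurses, n = 2 × (1.96 + 0.84)² / 0.7² = 32.0 by hand, 33 per group with unrounded quantiles, or 34 with the noncentral t. The stated 35 therefore reproduces, but only if nurses are treated as independent and hospital is ignored.

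**2. What 2 v 2 hospitals can show.** The number of ways to choose two of four hospitals is C(4,2) = 6. Even under random allocation, the smallest exact p-value is 1/6 = 0.17 one-sided and 2/6 = 0.33 two-sided. More nurses per hospital would not change this.

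**3. Clustering, a separate matter.** The documents give no intraclass correlation (ICC), so 0.01 to 0.10 is assumed. With 35/2 = 17.5 nurses per hospital and total SD 1, a hospital mean has variance v = ICC + (1 − ICC)/17.5. The difference between two averages of two hospitals has variance v/2 + v/2 = v. A nurse-level t test instead uses a standard error of √(2/35) = 0.239. Its true type I error is about 2 × [1 − Φ(1.96 × 0.239/√v)].

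| ICC | √ICC (SD of group difference from hospitals alone) | √v | 1.96 × 0.239/√v | Type I error | Power for 0.7 SD, hospital means, 2 df |
|---|---|---|---|---|---|
| 0.01 | 0.10 | 0.258 | 1.82 | 6.9% | 34% |
| 0.02 | 0.14 | 0.276 | 1.70 | 8.9% | 31% |
| 0.05 | 0.22 | 0.323 | 1.45 | 14.7% | 24% |
| 0.10 | 0.32 | 0.389 | 1.20 | 22.9% | 19% |

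A simulation with 17 nurses per hospital (20,000 runs) gave 7.1%, 8.7%, 14.5% and 22.4%, in agreement with the formula.

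**4. Width of an honest interval.** On hospital means there are 2 degrees of freedom, with t quantile 4.303. For a strand 2 difference the half-width is about 4.303 × 0.239 = 1.03 SD at ICC 0 and 4.303 × 0.389 = 1.67 SD at ICC 0.10, against a target of 0.7 SD. The width for a difference in change also depends on how strongly the two surveys correlate within hospital, which is not given.

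**5. A ranking of hospitals is not a test.** If the workshops do nothing and the hospitals are exchangeable, A and B both improve more than C and D with probability 1/6 = 17%.

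**The case against.** **The claim is already hedged.** The formal aim is descriptive. Principal Findings asks to what extent, if at all, the intervention works. Experimental, beside embedded, is a mixed methods term with citations. Potential Limitations lists confounding, maturation and unplanned events. Setting, Sampling, and Participants adds that "The hospitals chosen are of similar size, with similar service availability and case mix", with shared leadership and policies. All of this is fair and makes the overclaim milder. But no section says that allocation was non-random, or that two hospitals per group prevent attribution, and the effectiveness and efficacy wording stands beside the descriptive aim.

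**Stronger readings that the text does not support.**

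- A reader might infer that A and B were picked by the organisation's roll-out plan. Stakeholder Engagement ties that plan to which hospitals were included. How two of them became workshop sites is not stated.
- A reader might infer that a nurse-level p below 0.05 will be declared proof. The protocol states no such rule, and says that statistician support will be sought.
- A reader might take the 7% to 23% as the effect of non-random assignment. It is not. It measures ignored clustering at assumed ICCs and would be the same in a randomised 2 v 2 study. A full analysis plan, not shown, could also handle it.
- A reader might think a draw by lot would cure the problem. Assignment is reported in the past tense, and the limit of 0.33 holds under randomisation too.

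**Conclusion.** The concern holds as one of claim and comparison, not of arithmetic. The sample size reproduces for independent nurses. Two hospitals per group, no described randomisation and a strand 2 comparison without baseline cannot separate a workshop effect from hospital differences or local change, so the effectiveness and efficacy wording goes further than the design.

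The 0.33 limit rests only on the count of hospitals. The type I error of about 7% to 23% rests on an assumed ICC of 0.01 to 0.10, 35 nurses per group spread equally over two hospitals, and a t test that ignores hospital. The absence of randomisation is judged from a condensed article, but the article itself uses the causal wording without giving a basis for it.

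**What to change.** - **Label.** In the Abstract (Methods) and The Study Design, describe the quantitative component as a non-randomised (quasi-experimental) controlled before-and-after comparison with two hospitals per group.
- **Allocation.** In Setting, Sampling, and Participants, add a sentence on how A and B were chosen.
- **Claim.** In the Abstract (Results) and the Conclusions, replace the effectiveness and efficacy wording with a preliminary estimate of association.
- **Analysis.** In Quantitative Data Analysis, use the strand 1 survey: show the four hospital-level changes (strand 2 minus strand 1), the between-group difference in change, and a confidence interval that takes hospital into account. Hospital means suffice, so respondents need not be linked across surveys. State that the respondents may differ between the two occasions, and that local change over time is still not removed.
- **Consistency check.** Whether both A and B improve more than both C and D may be shown descriptively, but not used as a rule for claiming support.

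The cost is some rewording and one table or plot from data already being collected. The downside is a more modest claim and a wide interval.

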### Quantitative Data Analysis

The quantitative data will be analyzed using Stata 14 (TM; StataCorp LP), a statistical software that enables users to analyze, manage, and produce graphical presentations of data [38]. Participant characteristics will be summarized separately for intervention and control sites. Differences between groups for categorical variables will be assessed using chi-squared tests (or Fisher exact, the nonparametric equivalent) and Student's *t* tests for continuous variables. Differences between intervention and control sites in exposure to bullying (as assessed by the NAQ-R) and ways of coping (as assessed by the WCQ) will be assessed for all nurses at strand 2. Statistician support will be pursued to assist with analysis.

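### The stated 80% power at 5% type I error treats nurses as independent, but allocation is by hospital with two hospitals per arm, so the two figures do not hold together unless the ICC is near zero

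*Protocol article*

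**What the plan says.** All of this is in the protocol article.

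- *Setting, Sampling, and Participants* makes the hospital the unit of allocation: "The participants will be allocated into clusters according to hospitals at which they are working". The same section says that "2 of the 4 hospitals were assigned to have the Respectful Workplace Workshops delivered". The other two are controls.
- The sample size statement in that section assumes a 5% type I error and "80% power to detect an effect size equivalent to 0.7 of the SD", and concludes that it is necessary to "recruit 35 participants from the hospitals where the Respectful Workplace Workshops will be delivered and 35 from those where no workshops are conducted". It expects a 30% response: "The total target population is 230 at the time of writing this paper", so 69 nurses.
- The statement gives no ICC, no design effect and no allowance for the number of hospitals.
- *Quantitative Data Analysis* compares intervention and control sites on the NAQ-R and the WCQ at strand 2. The only method it names for continuous outcomes is Student's *t* ("tests for continuous variables").
- *Potential Limitations* covers comparability of the groups, maturation, unplanned events and low response. It does not mention correlation of responses within hospitals.

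**The concern.** The power calculation counts nurses, while the workshops are allocated to hospitals. If nurses in one hospital answer more alike than nurses in different hospitals, the difference between arms carries between-hospital variation. A calculation for independent individuals leaves that out.

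The article itself gives reason to expect such correlation. The *Background* says that organisational culture and leadership style affect negative behaviour. *Principal Findings* describes closely knit hospitals and wards whose long-serving staff may set the tone, and says the research is more about the organisational level than about individuals. An ICC of essentially zero, which the statement needs, is nowhere argued.

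The stake runs in both directions. *Conclusions* expects the comparison to give insight into the efficacy of the workshops and to inform policy. If the analysis allows for hospital, a null result is weaker evidence against a 0.7 SD effect than 80% power implies. If it does not, a significant result is weaker evidence for an effect than a 5% level implies.

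**Working it through.** **Inputs from the article:** difference 0.7 SD, type I error 5%, power 80%, 35 nurses per arm, 2 hospitals per arm.

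**Assumptions:**
- The test is two-sided. The article does not say, but one-sided would need 26 per arm, which does not match 35.
- Respondents split equally, so m = 35/2 = 17.5 per hospital.
- The SD is the total SD.
- ICC is 0.02, 0.05 or 0.10, because the article gives none.

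**1. The article's figure.** n per arm = 2(1.960 + 0.842)²/0.7² = 32.04, so 33. With the noncentral t distribution, power is 80.0% at 33, 81.2% at 34 and 82.3% at 35 per arm, and 34 is the smallest n that reaches 80%. The stated 35 is therefore the answer for independent individuals, with nothing added for clustering.

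**2. How much clustering the margin absorbs.** With normal critical values, power falls to 80% when 35/DE = 32.04, where DE = 1 + (m − 1)·ICC is the design effect. So DE = 1.092 and ICC = 0.092/16.5, about 0.006.

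**3. A test that allows for hospital.** Effective n per arm = 35/DE, and the noncentrality is 0.7·√(effective n/2). Power is shown with normal critical values (1.96), then with the t critical value on 2 + 2 − 2 = 2 df (4.30). The detectable effect at 80% power is 2.802·√(2·DE/35), before any df penalty.

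| ICC | DE | Effective n per arm | Power, normal | Power, 2 df | Detectable effect (SD) |
|---|---|---|---|---|---|
| 0 | 1.00 | 35.0 | 83% | 37% | 0.67 |
| 0.02 | 1.33 | 26.3 | 72% | 31% | 0.77 |
| 0.05 | 1.825 | 19.2 | 58% | 24% | 0.90 |
| 0.10 | 2.65 | 13.2 | 44% | 19% | 1.09 |

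The normal column is optimistic, because it treats the between-hospital variance as known when only four hospitals inform it.

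**4. Student's t test without adjustment.** Its standard error is too small by a factor of about √DE, so the true type I error is about 2[1 − Φ(1.96/√DE)]: 8.9%, 14.7% and 22.9%. Simulating 70 nurses in 2 + 2 hospitals gives:

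| ICC | Type I error | Rejection at 0.7 SD |
|---|---|---|
| 0.02 | 9% | 79% |
| 0.05 | 15% | 76% |
| 0.10 | 24% | 73% |

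**5. Whether more nurses would help.** With k = 2 hospitals per arm and normal critical values, n per arm = 33(1 − ICC)/(1 − 33·ICC/2).
- ICC 0.02: 32.34/0.67 = 48.3, so 49.
- ICC 0.05: 31.35/0.175 = 179.1, about 180. An equal split of the 230 gives only 115.
- ICC 0.10: the denominator is negative, so no number of nurses reaches 80%.

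**The case against.** The strongest reply is that the calculation is correct for what it computes and that the ICC range is the reviewer's. Both points are true. There is no slip of arithmetic here; the independence assumption does not match the allocation. The hospitals share executive leadership, policies, size and case mix, which could mean a low between-hospital ICC. But the statement survives only below about 0.006, and *Principal Findings* points the other way.

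It can also be said that the number of sites followed from the organisation's delivery plan (*Stakeholder Engagement*), and that the experimental part is embedded in a mixed methods study. That explains four hospitals, but it does not support the power figure attached to them. Nor can the matter be left to a fuller document, because the article itself states alpha, power, effect and sample size. The absence of a fully specified cluster model is not the complaint.

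A reader might infer more than the article supports:

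- *The study will simply miss a 0.7 SD effect.* That holds only for an analysis that allows for hospital. Under the one test named, rejection stays at 73% to 79%, and the larger failure is the type I error.
- *The whole fall to 31%, 24% and 19% comes from the omitted design effect.* The hospital-level test on 2 df has only about 37% power at ICC 0, so most of the fall comes from having four hospitals.
- *The expected 69 falls short of 70, and removing the 9 possible earlier attendees makes it worse.* The gap is immaterial: 33 per arm, or 66 nurses, still gives 80.0% on the article's own assumptions. The article does not say whether those 9 are within the 230.
- *Clustering by ward is the milder and correct case.* The article reports "This study included 12 wards or units across 4 nonmetropolitan, regional acute care hospitals" but no split by arm. If 6 wards per arm are assumed, with clustering by ward only and 10 df, power is 71%, 66% and 58% at the same ICCs, which is still below 80%.

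**Conclusion.** The concern holds. With 35 + 35 nurses in 2 + 2 hospitals, the design does not deliver 80% power and a 5% type I error together unless the ICC is below about 0.006. Allowing for hospital keeps the error rate and loses the power; ignoring hospital roughly keeps the rejection rate and loses the 5%. That one of the two figures fails does not depend on which ICC in the assumed range is taken. The size of the failure does, and it also rests on the equal split per hospital and the two-sided test. The article's 35 is correct for independent nurses, and the study is not shown to need more of them.

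**What to change.** In *Setting, Sampling, and Participants*, remove the unqualified statement of 80% power at 5% type I error. In its place:

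1. Say that 35 per arm is the size for independent nurses, and that allocation is to four hospitals, two per arm.
2. For about 69 respondents, give power for 0.7 SD (or the detectable effect) and the type I error over a stated ICC range, such as 0.02 to 0.10, for an analysis that accounts for hospital. The figures above for 70 serve almost unchanged: at ICC 0.02, 34.5/(1 + 16.25 × 0.02) = 26.0 effective nurses per arm, against 26.3.
3. If a ward-level variant is shown, state the split of wards by arm or mark it as assumed.
4. State that neither a null nor a positive between-site result should be read as coming from a test with 80% power and a 5% level.

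The cost is one paragraph and a less favourable stated figure. No participants, hospitals or data collection change.
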